### Patient allocation/randomisation sequence/blinding

All newly admitted patients will be checked by the nurse in charge at admission to ascertain whether they fit the inclusion criteria. If so, they will be given research information in written format and verbally by the same nurse at admission. On the next day they will be asked for informed consent (by the same nurse) and if they agree, the nurse will immediately call the central research office to find out to which group the patient has been randomized. Thus, the therapy according to randomization status will start immediately and within less than 48 hours after admission.

To ensure concealment of allocation, a randomization scheme was created in SPSS by assigning the intervention to a random sample of circa 50% in a list of 1,500 numbers and assigning the control group to the rest. This allocation of the group (sheepskin, usual care) was then blinded on a paper list numbered 1 through 1,500 by a secretary not further involved in the project. Each time a patient is admitted, the principal investigator located at the central research office is called. The above list with numbers and blinded allocation is held at this office. This central research office registers each patient identity for every consecutive number and discloses the group allocation to the nurse and patient.

Only the patient allocation itself is blinded to all parties involved, because it is impossible to blind health professionals or patients to whether someone is in the sheepskin group or not.

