### Intervention

The experimental condition consists of the application of the Australian Medical Sheepskin as an overlay on top of the standard/usual mattress in the area of the buttocks and in the (wheel)chair, combined with all care as usual. An extra Australian Medical Sheepskin at the bottom of the bed is also permitted. The intervention will start no later than 48 hours after admission. The Australian Medical Sheepskin will be applied during the first 30 days after admission (and prolonged if the patients wish so, but without gathering research data). The period of 30 days is chosen because most pressure ulcers develop in the first weeks after admission [6,10,36,37]. The sheepskins will be changed at least every two days.

Besides the use of the Australian Medical Sheepskin, all other usual pressure ulcer preventative interventions such as mobilization and repositioning may be added as co-interventions, in so far as they are normally used in the participating nursing homes. All other nursing care can be continued as usual (including incontinence materials).

The control group will receive usual care, including all the pressure relieving interventions and other preventive actions, normally taken in the participating nursing homes. The application, in any way, of the Australian Medical Sheepskin is forbidden in this group.

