### Outcomes

A distinction can be made between variables relating to the effectiveness (incidence, prevalence of pressure ulcers) and variables relating to costs (purchase and washing of the sheepskins on the one hand, and investment of time and materials cost for pressure ulcer treatment on the other). Both of these are necessary to compute cost-effectiveness.

The primary outcomes for this study are:

- the incidence of sacral pressure ulcers in the first 30 days after admissions,

- the costs of appliance of the sheepskin, and

- the costs related to treatment of the pressure ulcers that have developed.

Secondary outcomes are the presence of pressure ulcers on other places, quality of life, comfort of the sheepskin as experienced by the patients and ease of use of the sheepskin as experienced by the care personnel.

Influencing factors that will be measured are patient characteristics, the application of other pressure relieving interventions and materials and the use of incontinence materials.

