### Instruments

These outcomes, as well as influencing factors, will be measured by appropriate instruments, as far as possible we will use already existing and validated instruments. The EPUAP grading system is used to assess the presence and severity of pressure ulcers [38].

To this end a 'daily observation checklist' has been developed. Nurses use this checklist during the first 30 days after admission to report the presence/absence of sacral pressure ulcers, as well as the ulcer grade; the presence/absence of pressure ulcers on other locations and whether a sheepskin, repositioning, other support surfaces and incontinence material are applied.

When nurses feel uncertain about their observations they are instructed to call another specialized nurse, experienced in observing pressure ulcers.

Furthermore, a photographic series of the various pressure ulcer grades is available on each ward, as well as special glasses that can be used in order to differentiate better between blanchable and non-blanchable erythema. Finally, all nursing homes are offered a lesson in pressure ulcer observation.

The daily skin observations by nurses during routine care will be checked weekly by an experienced nurse observator from the nursing home itself and bimonthly by the principal investigator from the central research office.

Influencing patient factors that will be measured are age, gender, principal medical diagnosis category, surgery in the last month, presence of pressure ulcers at admission on other places than the sacrum, incontinence status, nutritional status (including body mass index), activity of daily living level (Barthel-index) and pressure ulcer risk score (Braden-scale). These are measured twice: at admission and at day 30 after it.

Furthermore the patients in the sheepskin group are asked at the end of the research period to rate the (dis)comfort of the sheepskin. For this purpose, a self-developed 7-item questionnaire with a 5-point rating answer structure was developed.

Data about costs that will be gathered are the costs of buying sheepskins, costs of washing sheepskins, costs of treatment of pressure ulcers (medication, wound care materials, diagnostics, kind of specialized consultants and time involved, and extra time for nurses/carers with regard to pressure ulcer treatment).

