### Data-analysis

First of all the primary outcomes will be analyzed using descriptive methods.

Statistical testing of differences in incidence and prevalence between experimental and control groups will be conducted by a two-sided Chi-square test. In addition, differences in number of pressure ulcer free days will be tested with a two-sided t-test for independent samples; and differences in onset of pressure ulcers will be analyzed with Kaplan Meier curves. All analyses will be controlled for influencing factors. Moreover, a multi level analysis will be performed because of the fact that data are gathered from several organizations and nursing wards.

Both intention-to-treat-analysis and per-protocol-analysis will be carried out.

The economic data about costs will be used in a model approach to show the economic consequences on a higher level. The aim is to develop a model that can show the consequences of implementing improved pressure ulcer care for an average nursing home and/or the national level.

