## Discussion

This study is innovative because it is the first to assess the cost-effectiveness of the Australian Medical Sheepskin in nursing home patients and also because current opinions and guidelines [13,41-44] oppose the use of sheepskins. However, these are based on old forms of sheepskins, not comparable to the genuine Australian Medical Sheepskin.

A difficult point in this research is that the usual care can not be standardized. Although nurses and nursing homes may have pressure ulcer protocols and say that they are following these, there is a chance that the usual care differs from nursing home to nursing home, or even from nursing ward to nursing ward, and that individual nurses may deviate from the protocol. Moreover, it is known that different mattresses are in use in and between nursing homes. Since standardization is in no way possible, a registration of mattresses and devices applied will be conducted.

With regard to possible contamination between experimental and control group, the following measures will be taken: clear instruction to all nursing and care personnel and patients, a limited stock of sheepskin on the ward, daily inspection of the skin by the research team in both groups, and a concise control and observation to ascertain whether the patients are still being nursed in the condition they were randomized to. Moreover it is not very likely that patients from both groups will be nursed on the same room during the same period (1.2 admissions per bed); therefore it is improbable that patients from the control group will ask for a sheepskin.

Finally, in the information sessions with nurses, it will be stressed that the Australian Medical Sheepskin is NOT a replacement for the normal pressure relieving interventions such as repositioning and other methods.

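### Adjusting all analyses for co-interventions recorded after randomisation can bias the adjusted sheepskin estimates in either direction

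*Protocol article*

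**What the plan says.** All references are to the protocol article.

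- **Data-analysis** names a two-sided chi-square test for incidence, a t-test for ulcer-free days and Kaplan-Meier curves for onset. It then sets a general rule: "All analyses will be controlled for influencing factors". It adds a multilevel analysis for organisations and wards, and plans both intention-to-treat and per-protocol analyses.
- **Outcomes** gives the term its content: "Influencing factors that will be measured are patient characteristics, the application of other pressure relieving interventions and materials and the use of incontinence materials".
- **Instruments** gives the timing. "Nurses use this checklist during the first 30 days after admission to report the presence/absence of sacral pressure ulcers", and on the same form they record "whether a sheepskin, repositioning, other support surfaces and incontinence material are applied". Of the patient factors (among them incontinence status, nutrition, Barthel and Braden), it says: "These are measured twice: at admission and at day 30 after it".
- **Intervention** leaves co-interventions to care staff: "all other usual pressure ulcer preventative interventions such as mobilization and repositioning may be added as co-interventions".
- **Patient allocation/randomisation sequence/blinding** accepts that "it is impossible to blind health professionals or patients to whether someone is in the sheepskin group or not". It has allocated care start within 48 hours of admission.
- **Discussion** reports that in staff sessions "it will be stressed that the Australian Medical Sheepskin is NOT a replacement for the normal pressure relieving interventions".

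**The concern.** The stated aim is the effect of adding the sheepskin to usual care, compared with usual care alone. What staff do with repositioning, other surfaces and incontinence materials after allocation is part of what is being compared. Such a variable can be a consequence of the arm, or a marker of skin that is already breaking down. Adjusting for it then stops the arms being compared as randomised.

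The two likely mechanisms pull in opposite directions. If care is stepped up when skin deteriorates, adjustment removes part of a real benefit. If staff use fewer other devices for sheepskin patients, adjustment credits the sheepskin with a benefit that the policy of adding it did not deliver. The article regards a 10-point absolute reduction as clinically significant, so a shift of one or two points in an adjusted risk difference can matter.

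This is not a detail left to an analysis plan. The article names the covariate set and applies it to every analysis. A plan that follows it inherits the problem, and a plan that departs from it contradicts the article.

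**Working it through.** **1. Tracing the rule.** Data-analysis adjusts for influencing factors, Outcomes includes co-interventions and incontinence materials among them, and Instruments records these daily for 30 days. Allocated care starts within 48 hours, so at least 30 - 2 = 28 of the 30 days fall after randomisation. No sentence limits the adjustment to admission values.

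**2. The plan's own figure, for reference.** For 28% vs 18% at two-sided 0.05, the standard two-proportion formula needs 277 per arm for 80% power. The planned 375 per arm gives 90.4%, which satisfies the stated minimum of 80%. This point does not rest on that figure.

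**3. Illustration A: care stepped up for deteriorating skin.** All inputs except 375 per arm are assumptions.
- Early skin deterioration: 40% control, 25% sheepskin.
- Ulcer risk: 62% with deterioration, 5% without.
- The co-intervention itself has no effect on ulcers.

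Ulcer risk by arm = d × 0.62 + (1 - d) × 0.05, where d is the proportion deteriorating:
- Control: 0.40 × 0.62 + 0.60 × 0.05 = 0.278
- Sheepskin: 0.25 × 0.62 + 0.75 × 0.05 = 0.1925
- Crude odds ratio = (0.1925/0.8075) / (0.278/0.722) = 0.619

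With co-intervention use of 70% in deteriorating patients and 20% in others, use by arm is:
- Control: 0.40 × 0.70 + 0.60 × 0.20 = 0.40
- Sheepskin: 0.25 × 0.70 + 0.75 × 0.20 = 0.325

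Use differs by arm only because the sheepskin prevented deterioration. A logistic model with arm and co-intervention, fitted to the expected counts, gives the following, with power ≈ Φ(|z| - 1.96):

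| Use if deteriorating / if not | Odds ratio | z | Power |
|---|---|---|---|
| Unadjusted | 0.619 | -2.75 | 78% |
| Adjusted, 60% / 40% | 0.625 | -2.67 | 76% |
| Adjusted, 70% / 20% | 0.667 | -2.21 | 60% |
| Adjusted, 80% / 10% | 0.736 | -1.58 | 35% |

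Rescaled to about the article's own 28% vs 18% (deterioration 40% vs 22.6%, ulcer risk 62.5% vs 5%), power starts at 90%. It becomes 88%, 75% and 47% in the same three cases.

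Adjusting for a predictor that is balanced between arms would normally move an odds ratio away from 1. Here it moves towards 1, so this is not merely the usual change of scale in an adjusted odds ratio.

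**4. Illustration B: a separate simulation.** 400,000 patients, assumed parameters, risk differences (RD) standardised from logistic models.

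| Scenario | RD, admission risk only | RD, adding device use |
|---|---|---|
| Use unrelated to arm, not caused by ulcer | -0.083 | -0.083 |
| Moderate substitution | -0.068 | -0.078 |
| Strong substitution | -0.046 | -0.070 |
| Devices added after an ulcer | -0.095 | -0.083 |

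Adjusting for admission risk alone matched the unadjusted RD to within 0.0003 in all four scenarios. Under strong substitution the odds ratio moved from 0.72 to 0.60. With devices added after an ulcer, the conditional odds ratio hardly moved (0.556 to 0.557) although the RD shrank.

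**5. Day-30 scores.** If a score that worsens after an ulcer were added to the admission-risk model, the RD would shrink by about 21% to 23% in the same scenarios (for example -0.083 to -0.066). This shows why a clarification is useful. It does not show that the plan does this.

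**The case against.** Four objections have weight.

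- **Bias is conditional.** A reader might infer that the rule necessarily biases the result. It does so only if co-intervention use depends on the arm or on emerging skin damage. The first simulated scenario shows no shift, and the instruction to staff not to replace normal measures is meant to limit substitution. This stands, so the claim is that the rule can bias. The instruction also shows that the authors saw substitution as a risk.
- **Day-30 scores.** A reader might infer that day-30 Braden or Barthel values enter the models. The article says only that they are measured. The list includes age and gender, so the phrase about measuring twice cannot apply literally to every item, and using admission values is an equally natural reading. This stands: day-30 values merit a clarifying phrase and are not a demonstrated fault.
- **Which result decides.** A reader might infer that the adjusted model carries the claim, because a chi-square test cannot be adjusted. The article names the chi-square test for incidence, and that comparison is unaffected. It also says that all analyses are controlled and does not rank the results. Neither reading can be established.
- **Selected inputs.** The fall to 35% power comes from steep assumed targeting. With 60%/40% use the loss is about two points. This stands, and the 35% should not be read as an expected loss.

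None of these removes the core: the defined covariate set includes variables recorded after randomisation, with no limit to admission values.

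**Conclusion.** The point holds in this form: the adjustment rule, read with the article's own definition and recording schedule, admits follow-up co-interventions and incontinence materials as covariates, and this can bias the adjusted estimates of the sheepskin effect. The direction is not fixed. Reactive care dilutes the effect and substitution exaggerates it.

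The size cannot be derived from the documents. In the assumed illustrations it runs from nothing, through an odds ratio moving from 0.62 to between 0.63 and 0.74, to a risk difference exaggerated by 2.4 points (-0.046 to -0.070). These results rest on assumed rates of deterioration, device use and device effect, and none of those is given in the article.

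The unadjusted chi-square comparison is sound in this respect. The exposure is that an adjusted result of uncertain meaning would stand beside it with nothing to say which one decides.

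**What to change.** Replace the general adjustment sentence in Data-analysis with wording such as:

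*Adjusted intention-to-treat analyses will use only factors recorded at admission, together with nursing home and ward. Co-interventions and incontinence materials used during follow-up, and scores measured at day 30, will not be covariates. Co-interventions will be reported by arm descriptively; any analysis that adjusts for them will be separate and labelled exploratory.*

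Admission factors already listed in Instruments can serve: age, gender, diagnosis category, recent surgery, non-sacral ulcers at admission, incontinence status, nutritional status, Barthel and Braden. Add one phrase saying whether the chi-square test or the adjusted analysis decides the primary comparison. The repair needs no particular model.

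The cost is wording only. The admission assessment is already completed for every eligible patient, the daily checklist already supplies the co-intervention data for description, and the sample size does not change.

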### Ethical considerations

Patients will be informed verbally and in written format about the research project before they are asked to participate and before they sign the informed consent form, which will also be signed by the nurse in charge at admission. At all times patients are free to stop their participation without having to give a reason for doing so.

The study protocol has been reviewed and approved by the certified Medical Ethical Review Board of the University Medical Centre of Utrecht (protocol number 06/287), on behalf of all the participating nursing homes.

The Board of directors of each participating nursing home signed a form in which they state they have read and understood the research protocol and that there are no obstacles at all to perform the research in their organizations.

The scientific merits of the study protocol have been reviewed in the consecutive phases of research funding process by the independent reviewers of the funding organization ZonMw, the Netherlands Organization for Health Research and Development [39]. The ZonMw grant obtained is number 945-07-513.

Next to this, the research protocol, and more specifically the washing procedure of the sheepskins, has also been judged by the Dutch Working Party on Infection Prevention [40] and has been approved as safe.

### Additional systematic reviews

In addition to the empirical data gathering, systematic literature reviews will be performed to retrieve adjuvant data concerning:

- costs of pressure ulcer treatment,

- pressure ulcer incidence and duration per grade in nursing home patients, and

- influence of pressure ulcers on quality of life.

These reviews will be conducted in order to compare the empirically found cost-effectiveness data to other studies, and to improve economic modelling and scenarios.

For these systematic reviews a protocol has been written including databases to be searched, search strategies, inclusion criteria and process, methodological assessment and data-analysis. These review protocols (in Dutch) can be obtained from the authors.

### Publication

All results from this study will be submitted to suitable peer reviewed journals and will be presented at appropriate international conferences.

The patient inclusion process started on May 1^st ^2007 and is expected to continue until the end of 2008. First results are not expected earlier than mid-2009.

## Discussion

This study is innovative because it is the first to assess the cost-effectiveness of the Australian Medical Sheepskin in nursing home patients and also because current opinions and guidelines [13,41-44] oppose the use of sheepskins. However, these are based on old forms of sheepskins, not comparable to the genuine Australian Medical Sheepskin.

A difficult point in this research is that the usual care can not be standardized. Although nurses and nursing homes may have pressure ulcer protocols and say that they are following these, there is a chance that the usual care differs from nursing home to nursing home, or even from nursing ward to nursing ward, and that individual nurses may deviate from the protocol. Moreover, it is known that different mattresses are in use in and between nursing homes. Since standardization is in no way possible, a registration of mattresses and devices applied will be conducted.

With regard to possible contamination between experimental and control group, the following measures will be taken: clear instruction to all nursing and care personnel and patients, a limited stock of sheepskin on the ward, daily inspection of the skin by the research team in both groups, and a concise control and observation to ascertain whether the patients are still being nursed in the condition they were randomized to. Moreover it is not very likely that patients from both groups will be nursed on the same room during the same period (1.2 admissions per bed); therefore it is improbable that patients from the control group will ask for a sheepskin.

Finally, in the information sessions with nurses, it will be stressed that the Australian Medical Sheepskin is NOT a replacement for the normal pressure relieving interventions such as repositioning and other methods.

With regard to treatment adherence, patients from the intervention group are asked only to keep the sheepskin in their bed for 30 days. No other action is required from patients other than actions that are also asked in the control group. However it remains possible that some patients after a few days will refuse the sheepskin (e.g. because of itching, not feeling comfortable, too hot, or other reason): in these cases the use of the Australian Medical Sheepskin will be stopped without persuading patients to continue, but they will be asked if the daily skin observations can be continued. Records will be kept of patients that have discontinued the use of the Australian Medical Sheepskin (including reasons to stop), and they will be analyzed in the group they were randomized, according to intention to treat analysis principles.

